# Home based exercise to improve turning and mobility performance among community dwelling older adults: protocol for a randomized controlled trial

**DOI:** 10.1186/1471-2318-14-100

**Published:** 2014-09-08

## Abstract

**Background:**

Turning is a common activity for older people, and is one of the activities commonly associated with falls during walking. Falls that occur while walking and turning have also been associated with an increased risk of hip fracture in older people. Despite the importance of stability during turning, there has been little focus on identifying this impairment in at risk older people, or in evaluating interventions aiming to improve this outcome. This study will evaluate the effectiveness of a 16 week tailored home based exercise program in older adults aged (50 years and above) who were identified as having unsteadiness during turning.

**Methods/Design:**

A single blind randomized controlled trial will be conducted, with assessors blind to group allocation. Study participants will be aged 50 years and above, living in the community and have been identified as having impaired turning ability [outside of age and gender normal limits on the Step Quick Turn (180 degree turn) task on the Neurocom® Balance Master with long plate]. After a comprehensive baseline assessment, those classified as having balance impairment while turning will be randomized to intervention or control group. The intervention group will receive a 16 week individualized balance and strength home exercise program, based on the Otago Exercise Program with additional exercises focused on improving turning ability. Intervention group will attend four visit to the assessment centre over 16 weeks period, for provision, monitoring, modification of the exercise and encourage ongoing participation. Participants in the control group will continue with their usual activities. All participants will be re-assessed on completion of the 16 week program. Primary outcome measures will be the Step Quick Turn Test and Timed-Up and Go test. Secondary outcomes will include other clinical measures of balance, psychological aspects of falls, incidence of falls and falls risk factors.

**Discussion:**

Results of this study will provide useful information for clinicians on the types of exercises to improve turning ability in older people with increased falls risk and the effectiveness of these exercises in improving outcomes.

**Trial Registration:**

ACTRN12613000855729.

## Background

Successful ambulation in one’s daily activities is dependent on the ability to maintain balance during navigation. Balance is defined as the “harmonious and contextually appropriate interplay of stability and mobility of the body with respect to its Base of Support” [1]. Impairments in balance, gait and lower limb strength are important factors associated with reduced mobility and dependency in activities of daily living among older people [2]. Balance performance results from a complex interaction between sensory and musculoskeletal systems requiring constant adjustment of muscle activity and joint position sense and other sensory information to retain the centre of mass of the body over the base of support [3]. In addition, disorders of motor output such as impaired (efferent) reaction time, reduced muscle strength and other factors such as pain can impair balance control [4]. Furthermore, impaired balance is one of the strongest risk factors for falls [5,6].

Turning is a common manoeuvre for older people, with one study reporting 20% of steps during indoor daily activities involving turning [7]. In a study evaluating turning in four activities, including walking through a cafeteria, through a convenience store, and from a specific office to a car in the parking lot, between 8-50% of steps involved a turning manoeuvre [8], highlighting the importance of turning in daily ambulation. Furthermore, turning has been shown to be a more challenging manoeuvre compared to straight-line walking [9]. Older people with balance impairment and history of falls have been shown to have difficulties during turning [10,11]. Falls during turning manoeuvres increase the risk of hips fractures eight times compared to falls during walking [12], and have also been found to be associated with greater risk of slip-related falls [13].

Exercise has been one of the most frequently investigated interventions to reduce falls among older people living in the community [14]. Meta-analyses have shown that exercise programs with a moderate to strong challenge to balance are most likely to be effective in improving functional and mobility performance among older adults, and to reduce risk of falling [14]. However, to date few studies have investigated turning difficulties in older people, and none have investigated the effect of an exercise program which includes specific exercises to improve turning ability in older people with identified turning impairment.

Therefore, the primary aim of the present study is to conduct a randomised controlled trial to evaluate the effectiveness of an individualized home based exercise program in improving turning and common balance impairments among community dwelling Malaysians aged 50 years identified as having impaired turning ability.

## Methods/Design

This study is a single blind randomized controlled trial, with the assessors blind to group allocation. The CONSORT statement has been used as a framework for development of methodology for this study [15]. A 16 weeks home based exercise program with a focus on exercises aiming to improve turning ability, as well as other identified balance impairments will be used for the intervention group, while the control group will maintain their usual activities. A flow diagram of the study protocol is illustrated in Figure 1.

**Figure 1 F1:**
[figure not shown]
Flowchart of study.

### Participants

Participants will be recruited from the membership of the University of Third Age (U3A) of Malaysia, on a voluntary basis. The age of 50 years and above will be used in this study as a criterion for defining “older people” (instead of the more commonly used age of 60 years and above), due to the lower life expectancy in Malaysia (72 years for males and 78 years for females [16]) compared to Western countries. Recruitment of participants will be through distribution of flyers to all U3A members.

Potential participants will be screened on a single occasion prior the baseline assessment to ensure they meet the study inclusion criteria. Participants will be included in the trial if they meet all of the inclusion criteria: i) identified having unsteadiness during turning Neurocom® Balance Master with long plate, and if performance is outside of normal limits (based on normative data based age and gender limits in the Neurocom® system); ii) community-dwelling; iii) aged 50 years and over; iv) able to tolerate standing and walking independently for at least six minutes and community ambulant (able to walk independently outdoors without support or not needing more than a single point stick; v) no other major neurological history (e.g. stroke with unilateral or bilateral paresis, multiple sclerosis) or orthopaedic history that impacts on functional mobility.

Participants will be excluded if they: i) have severe clinical or musculoskeletal impairments (eg; previous fractures) affecting mobility; ii) have visual or auditory impairments which cannot be corrected; iii) have a past history of stroke, Parkinson’s disease, cardiac problems, or transient ischemic attacks; iv) are aged less than 50 years old; v) use a walking frame, crutches or other bilateral support gait aids for walking in the community; vi) are not community ambulant (not able to walk outdoors away from home independently); and vii) are institutionalized (living in residential care).

### Measures and procedures

Participants will undergo a comprehensive assessment including questionnaires consisting of socio-demographic, health and medical conditions, assessment of falls risk, psychological aspects associated with falls, level of physical activity as well as balance and mobility assessment using clinical and laboratory (force platform) tests. Questionnaires will be interspersed between the physical performance tests, and participants will be able to rest between tests if required. A summary of the screening and assessment measures to be used is shown in Table 1.

**Table 1 T1:** Summary of the screening and assessment measures during baseline and after 16 weeks intervention program

**Screening tests**	**Baseline**	**Follow-up (16 weeks)**
Questions: age; standing & walking; independent living; independent community ambulation with no more than single point stick	√	
Cognition (Elderly Cognitive Assessment Questionaire-ECAQ).	√	
Socio-demographic information	√	
Health conditions & medication use	√	
History of falls	√ (past 12 months)	Will be asked at each phone call follow up (preceding 3 weeks) and at 16 weeks (falls diary)

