### Follow up data collection

Intervention group participants will be asked to complete a daily log of their exercise participation, to be used to calculate exercise adherence. Both the intervention and control group will receive four phone calls interspersed over the 16 week period (weeks 4, 8, 12 and 16) by a researcher to obtain details regarding any falls that occurred between phone contacts.

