Finally, there has been little falls prevention intervention programs conducted in Malaysia, and there is some evidence to suggest that interventions effective in Western countries (where the majority of falls prevention research has been carried out) may not always be translatable to Asian countries [44]. Differences in socioeconomic, cultural, behavioral and environmental factors may all impact upon the likely success of interventions between different countries. This study will provide some valuable local data regarding risk factors for falls among older community dwelling Malaysians, and the acceptability of this type of home exercise program in the Malaysian context. This study is proposed to provide a basis for planning future fall prevention interventions of relevance to specific identified falls risk in the Malaysian population.

There are several elements of our proposed method that have been adopted to accommodate the limited timelines and resourcing available for the project. There is some debate in the research literature relating to the accuracy of self-report measures of physical activity, and that accelerometers provide a more objective and valid measure [45]. The Human Activity Profile self-report measure selected for use in this project has been extensively used in research, and has been shown to be reliable and valid [46]. The duration of follow up for this study was limited to immediately following the four months intervention, instead of the recommended 12 month follow up for fall prevention studies [47]. Falls data is being collected as a secondary outcome measure to inform future study power calculations, however the study is not powered to detect a significant difference on the falls measure. These limitations are not expected to impact on the overall project aim of evaluating the effectiveness of this exercise program in improving turning performance.

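### Table 1's 3-week falls recall contradicts phone calls made 4 weeks apart to capture all falls between contacts

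*Protocol article*

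**What the plan says.** Two places in the protocol article define how falls are collected during follow-up.

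- **Measures and procedures, Table 1, row on history of falls.** The follow-up column reads "Will be asked at each phone call follow up (preceding 3 weeks) and at 16 weeks (falls diary"). The recall window at each call is therefore 3 weeks, with a falls diary as a second source at 16 weeks.
- **Follow up data collection.** "Both the intervention and control group will receive four phone calls interspersed over the 16 week period (weeks 4, 8, 12 and 16"), and a researcher makes them "to obtain details regarding any falls that occurred between phone contacts". The window is therefore the whole interval between calls.

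On the role of the data, the Abstract lists incidence of falls among the secondary outcomes. The Discussion says: "Falls data is being collected as a secondary outcome measure to inform future study power calculations". The sections on the primary outcome measure and the Discussion both say that the study is not powered for a difference in falls.

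**The concern.** The table and the text give different instructions for the same question at the same call. With calls 4 weeks apart, a question limited to the preceding 3 weeks skips the first week after each previous contact, whereas a question about everything since the last contact skips nothing. A call script built from the table would collect different data from one built from the text.

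What is at stake is the fall rate itself. The study does not expect to show a difference in falls, but it intends to pass its falls data on to the planning of later trials. For that use, the count and the exposure time it refers to must match. If the count comes from 12 weeks of recall and the denominator is 16 weeks, the rate is too low.

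**Working it through.** **Inputs**

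- Call times: weeks 4, 8, 12 and 16 (Follow up data collection).
- Recall window: 3 weeks (Table 1), or the interval between contacts, which is 4 weeks (Follow up data collection).
- Follow-up: 16 weeks = 16 × 7 = 112 days. The first interval is counted from the start of the 16 weeks.

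The article states no coverage figure, so there is none to reproduce.

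**Days covered by the calls**

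Each call covers the days from (call time − window) to the call time.

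| Call | Interval since last contact | Covered by a 3-week window | Not covered |
|---|---|---|---|
| Week 4 | days 1–28 | days 8–28 | days 1–7 |
| Week 8 | days 29–56 | days 36–56 | days 29–35 |
| Week 12 | days 57–84 | days 64–84 | days 57–63 |
| Week 16 | days 85–112 | days 92–112 | days 85–91 |

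- 3-week window: 4 × 21 = 84 days covered; 112 − 84 = 28 days uncovered; 28/112 = 25%.
- 4-week window: 4 × 28 = 112 days covered; 0 days uncovered.

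**Effect on the fall rate, under stated conditions**

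Suppose that callers use the table's window, that the diary recovers none of the falls in the uncovered weeks, that falls occur at a constant rate r, and that counts are divided by 16 weeks. Then

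reported rate = r × 12/16 = 0.75 r,

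which is an understatement of 25%.

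Under the same conditions, a later trial sized for a fixed rate ratio with a simple Poisson model needs a fixed number of events, so its person-time is proportional to 1/rate. Planning with 0.75 r in place of r gives 1/0.75 = 1.33 times the person-time needed.

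If any one of the first, second or fourth conditions fails, both figures shrink. With the text's window, or with a 12-week denominator for 12 weeks of recall, they vanish.

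**The case against.** The strongest reply is that the text governs. Follow up data collection is the procedural section, and under its rule all 112 days are covered. The table cell would then be a slip in wording with no effect on the data. This may well be the intention, but nothing in the article says which statement prevails, so the contradiction stands.

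A reader might also infer that a quarter of follow-up is never asked about. The documents do not support that. The same table cell adds a second collection, "and at 16 weeks (falls diary"), and the diary could pick up falls in the uncovered weeks. The article does not give the diary's period or format, but a condensed article commonly leaves such detail to the full protocol, so that is not a fault here. The 25% is a gap in the phone recall under one reading, and not an established loss of falls data.

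A third reply is that the consequence is small, and much of this stands. For illustration, 68 participants × 16/52 years is about 20.9 person-years at most. At assumed rates of 0.3 to 1.0 falls per person-year, that yields about 6 to 21 falls, with a Poisson relative standard error (1/√events) of about 40% to 22%. A 25% shortfall is then roughly 0.6 to 1.1 standard errors. Random error in the rate would be of similar size or larger. Unlike random error, however, the shortfall runs in one direction and costs nothing to prevent.

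Finally, the calls go to both groups. A recall window shared by both groups does not by itself distort a comparison between them, and no such bias is shown.

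**Conclusion.** The contradiction is certain on the face of the article: a 3-week recall in Table 1 against all falls between calls 4 weeks apart in the text. Read literally, the table leaves 4 of 16 weeks (25%) outside the phone recall, covered only if the 16-week diary captures them.

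The effect on the fall rate is conditional. An understatement of 25%, and a later trial about one third too large, is what follows if the table is followed, the diary adds nothing, falls occur at a constant rate and the denominator is 16 weeks. The article states no denominator for falls, so this is not the expected result. Step Quick Turn, Timed Up and Go and the sample size are untouched.

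This is an inconsistency between table and text in a secondary outcome. It is worth correcting because the rate is intended for later use, and because falls in an omitted week could not be reliably recovered afterwards.

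**What to change.** Change the follow-up cell for falls in Table 1, and the matching line of the call script, so that each call asks about falls since the last contact, in agreement with Follow up data collection. For the first call this means since the start of the 16 weeks. Use the same wording in both groups.

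The cost is one table cell and one line of the script. No extra calls, visits or participants are needed, and the analysis does not change.

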**Assessment – questionnaires/tests**		
Falls efficacy (fear of falling) – FES-I	√	√
Depression– Geriatric Depression Scale 15 items.	√	√
Visual contrast sensitivity (Melbourne Edge Test- MET)	√	
Activity level (Human Activity Profile Adjusted Activity Score - HAP-AAS)	√	√
Falls risk (FROP-Com risk assessment tool)	√	√
Exercise adherence (exercise diary)		√ (intervention group) daily exercise diary
**Assessments – clinical (balance/mobility)**		
Timed up and Go (single task)	√	√
Timed Up and Go (dual task)	√	√
Step Test (ST)	√	√
Functional Reach Test (FRT)	√	√
Five Times sit to stand Test (FTSS)	√	√
**Assessments – force platform**		
Modified Clinical Test of Sensory Interaction Balances (mCTSIB)	√	√
Limits of Stability (LOS)	√	√
Sit to Stand (STS)	√	√
Walk across (WA)	√	
Step quick turn (SQT)	√	√

All of the measures being used in this study have been shown to have moderate to high reliability and validity in a variety of older and clinical populations [17-20]. Assessments will be conducted by a trained assessor blind to group allocation.

Measures of fall risk and fall risk factors;

i. A retrospective recall about any falls in the preceding 12 months. The information regarding history of fall such as date, location, activity at the time of fall, obstacles involved in the fall, any warning sign or symptoms, type of injuries and medical attention sought after fall will be retrieved for each of fall event (details for up of 4 falls will be retrieved).

ii. Falls Risk assessment for Older People in the Community (FROP-Com) [19], a detailed assessment of 13 falls risk factors. Each domain of the assessment describes an evidence based fall risk factor among community dwelling older adults, and each domain is scored to reflect graded risk (nil, mild, moderate, severe). The FROP-Com has been shown to have good retest reliability (ICC for intra-rater and inter-tester reliability were 0.93 and 0.81 respectively) [21] and moderate accuracy predicting falls (sensitivity 71% and specificity 56%) [21]. A total score between 0 and 60 will be obtained, where higher scores indicate greater level of risk of falling.

iii. Activity level will be monitored in both groups at baseline and 16 weeks using the Human Activity Profile (HAP) [22]. The Adjusted Activity Score (AAS) will be used, calculated by subtracting the number of items listed as “stopped doing” from the highest numbered item listed as “still doing”. This will enable identification of any unanticipated change in activity/exercise level in the control group during the 16 week trial; as well as monitor any change in activity level by the intervention group.

iv. Psychological aspects related to falls will be measured using Falls Efficacy Scale-International (FES-I) short version-7 items [23] to assess the level of fear of falling. Level of depression will be measured using the 15 item Geriatric Depression Scale [24].

v. Visual contrast sensitivity will be evaluated using the Melbourne Edge Test (MET) [25]. The correct identification of the orientation of the edges on the circular patches provides a measure of contrast sensitivity in decibel units, where dB = −10log_10_ contrast.

Clinical balance and mobility measures to be administered at baseline will include:

i. Timed Up and Go Test (TUG) [26] will be used to measure dynamic balance and mobility. This assessment will be carried out by using a chair with armrests (seat height approximately 45 cm with armrest height 63 cm) and stop watch. The participant will be asked to stand up, walk 3 meters to a line on the floor at their usual speed, and return to a seated position in the chair. Participants will be allowed to use their usual gait aid used for indoors walking. The participant will be timed starting from when the instructor says “go”, and will stop when the participant sits again with their back against the back of the chair. The test will be repeated as a dual task test, using a secondary motor task by carry a cup of water. The time taken to complete the task is strongly correlated to level of mobility and activity of daily living performance [27].

ii. Lower body strength will be assessed using the Five Times Sit To Stand (FTSS) Test [20]. Participants will be asked to stand up and sit down from a 45 cm high chair five times as quickly as possible, with arms folded across their chest.

iii. Functional Reach test [28] is a dynamic test of standing balance in which the performance of reach ability in bilateral stance feet 10 cm apart will be evaluated. The participant will stand next to a wall with their feet 10 cm apart and dominant arm raised to 90 degrees. The initial distance of reach will be recorded. Then, participants will be asked to lean forward as far as they can without overbalancing and the distance of the additional reach will be recorded in centimetre (cm).

iv. Step Test [17] will be used to evaluate the speed of performing a dynamic repetitive single limb stance task (self-generated perturbation). The number of times the participant steps one foot fully on then off a 7.5 cm block step in 15 seconds will be recorded. Each foot will be tested separately. The worse side stepping (lowest score) will be used for analysis.

Laboratory assessment of balance related performance will be carried using Neurocom® Balance Master with long plate (Neurocom International, Inc.Clackamas, OR, USA). Practice trials will be provided on all tests to ensure the participant understands the test, prior to the actual measurement. All tests will be performed bare foot [29]. Five assessment procedures will be included:

I. Modified Clinical Test of Sensory Interaction of Balance (mCTSIB) -this test will measure the amount of sway under 4 sensory conditions (foot separation based on height, as detailed in user manual) [30] – eyes open and eyes closed on firm surface, and eyes open and eyes closed on a foam surface (medium density, 15 cm thick). Three trials are measured for each test, and the average sway from the three trials will be recorded. The composite sway velocity score (degrees/second), which was derived from the average of the sway velocity scores from the four sensory conditions, will be used in analyses.

II. Limits of stability (LOS) test (foot separation based on height, as detailed in user manual) [30] will be assessed to quantify the maximum distance and speed that a participant is able to intentionally displace their Centre of Gravity (COG), in shifting their weight towards eight targets positioned at 100% Limits of Stability. Maximum excursion (percentage of maximum limits of stability distance), which is the furthest distance of the center of gravity movement during testing, and directional control (percentage), which is a comparison of the amount of movement in the intended direction to the amount of extraneous movement, will be reported.

III. The Sit to Stand (STS) test will be used to quantify several movement characteristics as the participant rises from a seated to a standing position. The participant will sit on 41 cm high box placed centrally on the forceplate [30]. The participant’s feet are positioned equidistant from the center line. The participant will be instructed to hold steady until instructed to stand, and then to stand up quickly and to stand steady once upright. The sway exhibited during and immediately after performing the task (degrees/second) will be reported.

IV. The Walk Across (WA) test will be used to measure several characteristics of gait (gait velocity, step width, double support duration -% gait cycle) as the participant walks at comfortable pace across the long force plate [30].

V. The Step Quick Turn (SQT) test will be used to measure stability during 180 degree turn. The test involves the participant standing at one end of the long plate, and when instructed, to take one step with each leg (with a designated lead leg), then to turn 180 degrees quickly in the direction of lead leg, and return to the starting position, then to stand still [30]. Three trials will be repeated turning to the right, then three trials will be repeated turning to the left, and scores averaged for each direction of turning. Sway velocity (degrees/second) and turn time (s) will be reported for turning in each direction. For analysis, performance for the turn direction with worst performance (higher turn time or sway velocity) will be used.

Participants will be asked to wear an overhead harness as additional safety feature to prevent overbalancing during performing the modified CTSIB and Limits of Stability tests. The harness will be loose enough to allow normal balance reactions and upper body movement.

